# Study protocol: mycophenolate mofetil as maintenance therapy after rituximab treatment for childhood-onset, complicated, frequently-relapsing nephrotic syndrome or steroid-dependent nephrotic syndrome: a multicenter double-blind, randomized, placebo-controlled trial (JSKDC07)

**DOI:** 10.1186/s12882-018-1099-7

**Published:** 2018-11-01

**Keywords:** Mycophenolate mofetil, rituximab., frequently-relapsing nephrotic syndrome., steroid-dependent nephrotic syndrome., steroid-sensitive nephrotic syndrome., multicenter, double-blind, randomized, placebo-controlled trial.

## Abstract

**Background:**

Idiopathic nephrotic syndrome (INS) is the most common chronic glomerular disease in children. Approximately 80–90% of patients with childhood INS have steroid-sensitive nephrotic syndrome (SSNS), and can obtain remission with steroid therapy, while the remainder have steroid-resistant nephrotic syndrome (SRNS). Furthermore, approximately 50% of children with SSNS develop frequently-relapsing nephrotic syndrome (FRNS) or steroid-dependent nephrotic syndrome (SDNS). Children with FRNS/SDNS are usually treated with immunosuppressive agents such as cyclosporine, cyclophosphamide, or mizoribine in Japan. However, 10–20% of children receiving immunosuppressive agents still show frequent relapse and/or steroid dependence during or after treatment, which is defined as complicated FRNS/SDNS. Furthermore, 30% of SRNS patients who obtain remission after additional treatments such as cyclosporine also turn out to be complicated FRNS/SDNS. For such complicated FRNS/SDNS patients, rituximab (RTX) is currently used; however, recurrence after RTX treatment also remains an open issue. Because long-term use of existing immunosuppressive drugs has limitations, development of a novel treatment for maintenance therapy after RTX is desirable. Mycophenolate mofetil (MMF) is an immunosuppressive drug with fewer side effects than cyclosporine or cyclophosphamide. Importantly, recent studies have reported the efficacy of MMF in children with nephrotic syndrome.

**Methods:**

We conduct a multicenter, double-blind, randomized, placebo-controlled trial to evaluate the efficacy and safety of MMF after RTX therapy in children with complicated FRNS/SDNS. Patients are allocated to either RTX plus MMF treatment group, or RTX plus placebo treatment group. For the former group, MMF is administered at a dose of 1000–1200 mg/m^2^/day (maximum 2 g/day) twice daily for 17 months after RTX treatment. The primary endpoint is time-to-treatment failure (development of frequent relapses, steroid dependence or steroid resistance).

**Discussion:**

The results will provide important data on the use of MMF as maintenance therapy after RTX to prevent complicated FRNS/SDNS patients from declining into treatment failure. In future, MMF in conjunction with RTX treatment may permit increased duration of remission in ‘complicated’ FRNS/SDNS cases.

**Trial registration:**

This trial was prospectively registered to UMIN Clinical Trials Registry on June 23, 2014 (UMIN Trial ID: UMIN000014347).

## Background

Childhood-onset idiopathic nephrotic syndrome (INS) is the most common glomerular disease which occurs in more than 2 cases/100,000 children [1]. Notably, in Japan, the estimated incidence of INS is 6.49 cases/100,000 children annually [2]. Minimal change nephrotic syndrome is the most common form of the disorder, for which steroid therapy is effective for most patients [3]. Eighty to 90 % of patients achieve remission with the administration of steroids (steroid-sensitive nephrotic syndrome; SSNS) while 10–20% of patients suffer from steroid-resistant nephrotic syndrome (SRNS) which does not achieve remission with the administration of steroids [4].

Those who respond well rarely progress to end stage renal disease, but up to 50% of SSNS cases develop frequently-relapsing nephrotic syndrome (FRNS) [5]. FRNS is defined as at least four relapses per year or at least two within 6 months of the initial presentation (Table 2) [6]. A total of 50–60% of children with FRNS develop two consecutive relapses during tapering or within 14 days of stopping steroid therapy, this is termed steroid-dependent nephrotic syndrome (SDNS) (Table 2) [3, 6]. Treatment with immunosuppressive drugs is carried out to avoid the steroid-specific adverse event because each relapse requires a large dose of steroids. The Kidney Disease: Improving Global Outcomes Clinical Practice Guideline for Glomerulonephritis recommends alkylating agents, such as cyclophosphamide or chlorambucil, levamisole, calcineurin inhibitors, including cyclosporine or tacrolimus, and mycophenolate mofetil (MMF) as corticosteroid-sparing agents for children with FRNS/SDNS [7]. The clinical practice guidelines for pediatric idiopathic nephrotic syndrome (2013) recommend cyclosporine, cyclophosphamide, and mizoribine as immunosuppressive drugs for FRNS/SDNS [6]. Most children with FRNS/SDNS are effectively treated with these recommended immunosuppressant drugs; however, at least 10–20% of children receiving immunosuppressive agents still show frequent relapses or steroid dependence after treatment (complicated FRNS/SDNS). Additionally, some patients with SRNS develop steroid-sensitive frequent relapses or steroid dependence after achievement of complete remission by immunosuppressive therapies including calcineurin inhibitors (complicated FRNS/SDNS). A 5-year follow-up study of cyclosporine treatment in children with SRNS showed that 7 of 31 (23%) patients developed frequent relapses under immunosuppressive therapy after achievement of complete remission [8]. Meanwhile, the total dosage of cyclophosphamide is restricted due to gonadal toxicity and late-onset carcinogenicity, and we cannot use cyclosporine exclusively because cyclosporine can cause chronic nephrotoxicity as a side effect. However, discontinuation of cyclosporine often results in frequent relapses again [9, 10].

In that context, there have been many reports that rituximab (RTX), a monoclonal antibody directed against the CD20 differentiation antigen expressed on the surface of B cells, is effective and safe in children with complicated FRNS/SDNS [11–13]. Recently, RTX has been used for complicated FRNS/SDNS, although some cases tend to relapse after the recovery of B cell counts [14–16]. In addition, the safety of long-term B cell suppression caused by repeated administration of RTX in children whose immune system is developing is unknown. Therefore, a new maintenance therapy to prevent the relapse after RTX treatment is urgently needed.

Mycophenolate mofetil (MMF) is an immunosuppressant which selectively blocks de novo purine synthesis, a pathway crucial for both B and T lymphocytes, and has been used for various autoimmune diseases and as immunosuppressive therapy after organ transplantation [17–20]. In addition, it is reported that MMF is effective in childhood-onset nephrotic syndrome [21–30]. Our group has conducted a pilot study and reported that maintenance therapy with MMF after a single dose of RTX in complicated SDNS significantly prolonged the relapse-free period compared with RTX monotherapy [31]. Thus, MMF is a promising drug for maintenance therapy after RTX, however a prospective randomized clinical trial is still needed. [32] Therefore, we conduct a multicenter, double-blind, randomized, placebo-controlled trial to evaluate the efficacy and safety of MMF after RTX therapy in children with complicated FRNS/SDNS.

## Methods/design

A flow chart of the study design is shown in Fig. 1.

**Fig. 1 Fig1:**
[figure not shown]
Flow diagram of the clinical trial set-up. This trial is a multicenter, double-blind, randomized, placebo-controlled trial. After obtaining informed consent, registration and allocation is conducted. After rituximab treatment, mycophenolate mofetil or placebo is administered and the treatment key is opened following completion of the entire clinical trial

### Aim

The aim of this trial is to investigate whether RTX plus MMF combination therapy is superior to RTX alone for the maintenance of remission after RTX treatment in children with complicated FRNS/SDNS.

### Study design and patients

We conduct a multicenter, double-blind, randomized, placebo-controlled trial to assess the efficacy and safety of MMF after RTX therapy in children with complicated FRNS/SDNS (Fig. 1, Table 2 [6]). In total, 80 patients from 27 institutions in Japan will be enrolled in this study. We will diagnose NS and remission and relapse according to the International Study of Kidney Disease in Children (ISKDC) [6, 33]. Patients who are aged between 1 and 18 years old at the time of onset of idiopathic nephrotic syndrome and are aged 2 years or above at the time of registration are eligible if they fall into the complicated FRNS/SDNS category.

Inclusion and exclusion criteria are as follows:

Inclusion criteria:Diagnosed as INS according to the ISKDC criteria.The initial onset of INS is at between 1 and 18 years of age, and the patient is 2 years of age or older at assignment.Patients meeting one of the following criteria:Diagnosed with frequent relapse or steroid dependence and once again diagnosed with frequent relapse or steroid dependence after completion of immunosuppressive drug therapy (cyclosporine, cyclophosphamide, or mizoribine, etc.).Diagnosed with frequent relapse or steroid dependence and once again diagnosed with frequent relapse or steroid dependence during immunosuppressive drug therapy (cyclosporine, cyclophosphamide, or mizoribine, etc.).Diagnosed with steroid resistance following the onset of INS and diagnosed with frequent relapse or steroid dependence during or after the completion of immunosuppressive drug therapy (cyclosporine alone or combination of cyclosporine and methylprednisolone, etc.).Patients with records of the nearest preceding 3 relapses.Patients in whom steroid sensitivity is observed during treatment of relapse immediately prior to assignment.Patients in whom ≥5 CD20-positive cells/μL are observed in the peripheral blood.Patients who can be hospitalized overnight on the first day of rituximab administration.Written informed consent.

Exclusion criteria:Patients who have been diagnosed with nephritic-NS, such as IgA nephropathy, prior to assignment or in whom secondary NS is suspected.Patients who have used a monoclonal antibody other than rituximab.Patients meeting one of the following infection criteria:Presence or history of severe infections within 6 months prior to assignment.Presence or history of opportunistic infections within 6 months prior to assignment.Presence of active tuberculosis.Patients with a history of tuberculosis or in whom tuberculosis is suspected.Presence or history of active hepatitis B or hepatitis C or hepatitis B virus carrier.Presence of human immunodeficiency virus (HIV) infection.Presence or history of angina pectoris, cardiac failure, myocardial infarction, or serious arrhythmia (findings observed under Grade 4 of the Common Terminology Criteria for Adverse Events (CTCAE)).Presence or history of autoimmune diseases or vascular purpura.Presence or history of malignant tumor.History of organ transplantation.History of drug allergies to methylprednisolone, acetaminophen, or d-chlorpheniramine maleate.Uncontrollable hypertension.Deteriorated kidney function, e.g. estimated glomerular filtration rate (GFR) < 60 mL/min/1.73 m^2^.Having received a live vaccine within 4 weeks prior to enrollment.Patients showing one of the following abnormal clinical laboratory values:Leukocytes < 3000/μL.Neutrophils < 1500/μL.Platelets < 50,000/μL.Alanine aminotransferase (ALT) > 2.5× upper limit of normal value.Aspartate aminotransferase (AST) > 2.5× upper limit of normal value.Positive for hepatitis B surface (HBs) antigen, HBs antibody, hepatitis B core (HBc) antibody, or HCV antibody.Positive for HIV antibody.Patients who do not agree with contraception during the study period.Women during pregnancy or breast-feeding.Judged inappropriate for this study by the treating or study physicians.

### Randomization

Patients are randomly assigned to either RTX plus MMF, or RTX plus placebo group at an approximate ratio of 1:1 using the following allocation adjustment factors; medical institution, age, treatment history (presence or absence of immunosuppressive drug administration at the relapse immediately prior to enrollment, presence or absence of steroid administration at the relapse immediately prior to enrollment), interval between the last 3 relapses, presence or absence of history of SRNS.

Patients, their guardians, treating physicians, and individuals assessing outcomes and analyzing data are blinded to the patients’ assigned treatment. Apart from the data-monitoring committee, all treating physicians and other investigators remain blinded to the trial results until follow-ups are completed.

### Procedures

#### Observation period

The observation period is from the date the first dose of RTX is administered (day 1) to the date MMF administration is finished (day 505).

### Dosage regimen

RTX and the investigational drug (MMF or placebo) are administered in this trial. The dosage regimen is shown in Fig. 2. For the RTX plus MMF combination group, RTX is administered as 4 × 375 mg/m^2^ doses (maximum dose: 500 mg) given at weekly intervals and MMF is additionally administered at a dose of 1000–1200 mg/m^2^/day (maximum 2 g/day) twice daily after breakfast and dinner, continued for 17 months after RTX treatment. For the RTX plus placebo group, RTX is administered as 4× 375 mg/m^2^ doses (maximum dose: 500 mg) given at weekly intervals and the placebo is administered in place of MMF.

**Fig. 2 Fig2:**
[figure not shown]
Dosage regimen. Rituximab (RTX) and investigational drug (mycophenolate mofetil (MMF) or placebo) are administered in this trial. The date the first dose of RTX is administered is defined as day 1 and the date MMF administration is finished will be day 505. Calcineurin inhibitors (cyclosporine, tacrolimus) administered prior to registration for this clinical trial are administered in combination with the trial regimen and dosage at the time of registration until day 85 (however the dosage may be changed based on monitoring) and the dosage will be sequentially reduced every 28 days from day 86 onwards and discontinued approximately on day 169. MMF, mizoribine, azathioprine, cyclophosphamide, chlorambucil administered prior to the registration of this clinical trial, are discontinued on day 1. Prednisolone will be administered for treatment of relapse immediately prior to registration or during the observation period

The investigational drug can be begun at half the dose and increased to the defined dose in the absence of adverse reactions within 3 months. If patients cannot accept the full dose due to of adverse events, the doctors in attendance can decide the dose reduction. To prevent infusion reactions, patients receive a premedication with methylprednisolone, oral acetaminophen, oral d-chlorpheniramine maleate approximately 30 min prior to the administration of each dose of RTX [11].

### Prednisolone treatment for relapse at screening and during the study period

Participants receiving prednisolone for relapse at screening continue receiving the drug, taking 60 mg/m^2^ orally three times a day (maximum of 80 mg per day or 60 mg per day, depending on the institution policy) for 4 weeks. Participants with relapse not receiving prednisolone at screening receive the same dose until 3 days after complete remission is achieved. After 4 weeks (in patients who received prednisolone at screening) or from 3 days after complete remission (in patients who did not receive prednisolone at screening), patients take 60 mg/m^2^ prednisolone in the morning on alternate days (maximum 80 mg per day or 60 mg per day) for 2 weeks, then 30 mg/m^2^ on alternate days (maximum 40 mg per day or 30 mg per day) for 2 weeks, and then 15 mg/m^2^ on alternate days (maximum 20 mg per day or 15 mg per day) for 2 weeks. When patients have relapses during the study period, they receive 60 mg/m^2^ oral prednisolone three times a day (maximum 60 mg per day) until 3 days after complete remission is obtained, then take 60 mg/m^2^ prednisolone in the morning on alternate days (maximum 60 mg per day) for 2 weeks, then 30 mg/m^2^ on alternate days (maximum 30 mg per day) for 2 weeks, and then 15 mg/m^2^ on alternate days (maximum 15 mg per day) for 2 weeks.

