### Outcomes

The primary endpoint is defined as the time-to-treatment failure (development of frequent relapses, steroid dependence or steroid resistance). Diagnosis of FRNS, SDNS, and SRNS is based on relapse dates according to the ISKDC (Table 2). The secondary end points are time to relapse, relapse rate, time to FRNS, time to SDNS, time to SRNS, total steroid dose, peripheral blood B cell depletion period and adverse events. Adverse events are recorded throughout the trial period and assessed using CTCAE.

**Table 2 Tab2:** Definitions [6]

A. *Nephrotic syndrome*	The presence of a urine protein-to-creatinine ratio of 1.8 or above and serum albumin of 2.5 g/dL or below.
B. *Complicated nephrotic syndrome*	A patient that fulfills any of the following criteria is deemed to suffer from complicated nephrotic syndrome: (1) Diagnosed with frequent relapse or steroid dependence and once again diagnosed with frequent relapse or steroid dependence after completion of immunosuppressive drug therapy (cyclosporine, cyclophosphamide, mizoribine, etc.) (2) Diagnosed with frequent relapse or steroid dependence and once again diagnosed with frequent relapse or steroid dependence during immunosuppressive drug therapy (cyclosporine, cyclophosphamide, mizoribine, etc.) (3) Diagnosed with steroid resistance and diagnosed with frequent relapse or steroid dependence during or after the completion of immunosuppressive drug therapy (cyclosporine or combination of cyclosporine and methylprednisolone, etc.)
C. *Remission*	Negative protein on urine dipstick in the first morning urine for 3 consecutive days.
D. *Steroid sensitivity*	When the daily administration of prednisolone at 60 mg/m^2^/day leads to remission within 4 weeks.
E. *Relapse*	Protein 2+ or above detected by urine dipstick in the first morning urine for 3 consecutive days and prednisolone treatment is required.
F. *Frequent relapse*	Two or more relapses within 6 months after initial remission or 4 or more relapses within any 12-month period.
G. *Steroid dependence*	Two consecutive relapses during the reduction of steroid therapy or within 2 weeks of discontinuation of steroid therapy.
H. *Steroid resistance*	When the daily administration of prednisolone at 60 mg/m^2^/day does not lead to remission within 4 weeks.

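### The prednisolone section writes the daily dose as 60 mg/m² three times a day, where Table 2 of the same article gives 60 mg/m²/day

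*Protocol article*

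**What the plan says.** The article's section on prednisolone treatment for relapse at screening and during the study period sets the steroid course in a daily phase and three alternate-day steps.

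- Relapse at screening, already on prednisolone (daily phase lasting 4 weeks): "taking 60 mg/m^2^ orally three times a day (maximum of 80 mg per day or 60 mg per day, depending on the institution policy".
- Relapse at screening, not yet on prednisolone: "Participants with relapse not receiving prednisolone at screening receive the same dose until 3 days after complete remission is achieved". This group takes over the dose of the first.
- Relapse on study: "they receive 60 mg/m^2^ oral prednisolone three times a day (maximum 60 mg per day) until 3 days after complete remission is obtained".
- On-study taper: it begins "then take 60 mg/m^2^ prednisolone in the morning on alternate days (maximum 60 mg per day) for 2 weeks" and continues at 30 and 15 mg/m² with caps of 30 and 15 mg.
- Screening taper: its first step is 60 mg/m² with a cap of 80 or 60 mg; the second is "then 30 mg/m^2^ on alternate days (maximum 40 mg per day or 30 mg per day) for 2 weeks" and the third "and then 15 mg/m^2^ on alternate days (maximum 20 mg per day or 15 mg per day) for 2 weeks".

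Table 2, in the Outcomes section, gives the dose behind the definitions. Item D, steroid sensitivity, reads: "When the daily administration of prednisolone at 60 mg/m^2^/day leads to remission within 4 weeks". Item H, steroid resistance, uses the same 60 mg/m²/day. One inclusion criterion admits "Patients in whom steroid sensitivity is observed during treatment of relapse immediately prior to assignment"; it uses the Table 2 D term but states no dose.

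**The concern.** In both daily-phase phrases the amount per square metre has no per-day unit, nothing says that it is divided, and a frequency of three follows. Taken at its word, the instruction is three doses of 60 mg/m², which is three times the dose in Table 2 for the same treatment. All three daily-phase groups are affected, two directly and one by reference.

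This is not how the article writes divided doses elsewhere. In the Dosage regimen section, mycophenolate mofetil is given as an amount per m² per day, with a daily maximum, followed by the frequency.

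What is at stake is the amount of steroid a child is told to take. Patients are eligible from 2 years of age, so small children, in whom the daily cap may not bind, can be enrolled.

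**Working it through.** **Inputs.** Doses and caps come from the prednisolone section and the reference dose of 60 mg/m²/day from Table 2 D and H. The article gives no body-surface data, so the body sizes in step 3 are assumptions.

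**Step 1: the pattern in the plan's own caps.** The body size at which a cap starts to bind is the cap divided by the dose per m².

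| Step | 60 mg policy, and all on-study relapses | 80 mg policy (screening only) |
|---|---|---|
| Alternate days, 60 mg/m² | 60/60 = 1.00 m² | 80/60 = 1.33 m² |
| Alternate days, 30 mg/m² | 30/30 = 1.00 m² | 40/30 = 1.33 m² |
| Alternate days, 15 mg/m² | 15/15 = 1.00 m² | 20/15 = 1.33 m² |

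The ratio is constant within each policy.

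**Step 2: the daily phase under each reading.**

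- 60 mg/m²/day in total (20 mg/m² per dose): 60/60 = 1.00 m² and 80/60 = 1.33 m². This matches every taper step and Table 2.
- Literal, 3 × 60 = 180 mg/m²/day: 60/180 = 0.33 m² and 80/180 = 0.44 m². This matches neither, and the dose per m² would hardly matter because the cap would bind at very small sizes.

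**Step 3: what the difference would be with the cap applied.** Literal daily dose = min(180 × BSA, cap); intended daily dose = min(60 × BSA, cap), where BSA is body surface area in m².

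| Assumed BSA | Cap 60 mg: literal vs intended | Ratio | Cap 80 mg: literal vs intended | Ratio |
|---|---|---|---|---|
| 0.5 m² | 60 vs 30 mg | 2.00 | 80 vs 30 mg | 2.67 |
| 0.8 m² | 60 vs 48 mg | 1.25 | 80 vs 48 mg | 1.67 |
| 1.0 m² | 60 vs 60 mg | 1.00 | 80 vs 60 mg | 1.33 |
| 1.2 m² | 60 vs 60 mg | 1.00 | 80 vs 72 mg | 1.11 |
| 1.33 m² | 60 vs 60 mg | 1.00 | 80 vs 80 mg | 1.00 |

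The two readings agree from 1.0 m² upward under the 60 mg cap and from 1.33 m² upward under the 80 mg cap. The 80 mg columns apply only to the screening relapse, and only at institutions with that policy. No cumulative excess is given, because daily dosing on study lasts until 3 days after remission and so has no fixed length.

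**The case against.** The best reply is that the sentence corrects itself. The daily maximum stands directly beside the dose, and three full doses would exceed it in any child above 0.33 m² (60 mg) or 0.44 m² (80 mg). The phrase can also be read as a daily amount taken on three occasions, and Table 2 settles which amount. A paediatric nephrologist would probably dose correctly, and the article condenses a protocol that is not shown.

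Much of this stands. The intended dose can be recovered from the article, and the figures in step 3 describe a mixed reading, literal but cut back to the cap, at assumed sizes. The reply does not remove the error. Below 1.0 or 1.33 m² both readings stay within the cap and give different doses. A stated dose should not have to be inferred from its cap and a definitions table.

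Three stronger readings are tempting, and the article supports none of them.

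- A reader might infer that children received three times the intended dose. The cap rules that out above 0.33 or 0.44 m², and nothing shows that any site dosed from this sentence.
- A reader might infer that the wording contradicts the taper caps. It breaches none of them, since they govern the alternate-day steps. Their constant ratio is evidence of intent, not a second contradiction.
- A reader might infer damage to the steroid-resistance component of the primary endpoint or to the total steroid dose. Table 2 H is unambiguous, and any such effect would require literal dosing to have happened. The wording is the same for both arms and does not enter the sample-size calculation.

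**Conclusion.** The daily-phase dose is wrong as written in two places and carried into a third, and it conflicts with Table 2 D and H. The intended dose is 60 mg/m²/day in three divided doses; the choice of dose itself is not criticised. This is a wording error of the lowest severity.

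Any excess is hypothetical and is confined to children below the two body sizes at which the caps bind. It rests on two things the article does not provide: the body sizes of the participants, and whether the site-facing protocol has the same phrase. How many children fall below the thresholds therefore cannot be stated. No consequence for power, endpoints or comparability of the arms is claimed.

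**What to change.** In both places in the prednisolone section, replace the phrase with *60 mg/m²/day orally in three divided doses*. Keep the caps as they are: 80 or 60 mg per day by institution policy for the relapse at screening, and 60 mg per day for relapses on study. The sentence that refers to the same dose is then correct without change. Check the site-facing protocol for the same wording.

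The cost is two corrected phrases, plus a notice to sites only if their protocol carries the same wording.
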